## Abstract

**Background:**

Non-invasive electrotherapy is commonly used for treatment of chronic low back pain. Evidence for efficacy of most electrotherapy modalities is weak or lacking. This study aims to execute a high-quality, double-blinded randomized controlled clinical trial comparing 1) H-Wave® Device stimulation plus usual care with 2) transcutaneous electrical nerve stimulation (TENS) plus usual care, and 3) Sham electrotherapy plus usual care to determine comparative efficacy for treatment of chronic non-specific low back pain patients.

**Methods/Design:**

Patients- Chronic non-specific low back pain patients between ages of 18–65 years, with pain of at least 3 months duration and minimal current 5/10 VAS pain. Patients will have no significant signs or symptoms of lumbosacral nerve impingement, malignancy, spinal stenosis, or mood disorders.

Study design- Double blind RCT with 3 arms and 38 subjects per arm. Randomization by permuted blocks of random length, stratified by Workers Compensation claim (yes vs. no), and use of opioids. The null hypothesis of this study is that there are no statistically significant differences in functional improvement between treatment types during and at the end of a 12-week week treatment period.

Data collection- Subjective data will be collected using Filemaker Pro™ database management collection tools. Objective data will be obtained through functional assessments. Data will be collected at enrollment and at 1, 4, 8, and 12 weeks for each participant by a blinded assessor.

Interventions- H-Wave® device stimulation (Intervention A) plus usual care, transcutaneous electrical nerve stimulation (TENS) (Intervention B) plus usual care, and sham electrotherapy plus usual care (control). Each treatment arm will have identical numbers of visits (4) and researcher contact time (approximately 15 hours).

Outcomes- Primary outcome measure: Oswestry Disability Index. Secondary measures include: Rowland Morris Instrument, VAS pain score, functional evaluation including strength when pushing and pulling, pain free range of motion in flexion and extension. Outcome measures assessed at baseline, 1, 4, 8, and 12 weeks. Treatment failure will be defined if patient terminates assigned treatment arm for non-efficacy or undergoes invasive procedure or other excluded cointerventions. Data will be analyzed using intention-to-treat analysis and adjusted for covariates related to LBP (e.g. age) as needed.

**Discussion:**

Study strengths include complex randomization, treatment group allocation concealment, double blinding, controlling for co-interventions, rigorous inclusion criteria, assessment of compliance, plans for limiting dropout, identical assessment methods and timing for each treatment arm, and planned intention-to-treat analyses.

## Background

Low Back Pain (LBP) is one of the most common reasons for medical visits to physician offices and emergency departments, with an estimated 61 Million visits in 2007, up from an estimated 15 million visits in 1990 [1-3]. Chronic low back is associated with significant comorbidity and direct health care costs due to increased health care utilization [4]. The economic burden of low back pain is estimated between $20 and $50 billion annual cost to the U.S. economy [5]. Additionally, low back injuries result in an estimated 149 million lost workdays per year and an additional $28 billion in productivity losses [6]. Despite the relative pervasiveness of low back pain, and the enormous financial burden on the health care system, chronic low back pain remains a difficult condition to treat [7,8]. Identification of efficacious noninvasive, nonpharmacologic therapies could yield meaningful gains and result in substantial population improvement in morbidity and costs associated with LBP. A well-designed randomized trial is needed to determine comparative treatment efficacy of electrical stimulation treatments that are relatively inexpensive, noninvasive and nonpharmacologic.

Myriad treatments have been described for chronic LBP, yet the body of quality randomized trials demonstrating efficacy for many commonly used treatments is limited [9-11]. A recent evidence based review demonstrated that only 47 of 148 treatment interventions for Chronic LBP have quality randomized trials as the basis of recommendation for the intervention for low back pain [8]. Thus, the majority of commonly used interventions have little or no evidence of efficacy.

Specific to electrotherapy modalities, multiple devices producing varying electronic waveform types, wave frequency, and wave amplitude are used for analgesic relief of chronic pain conditions, including nonspecific low back pain. An evidence based review of electrotherapy literature identified a modest number of moderate and low quality trials that demonstrated evidence of transcutaneous electrical nerve stimulation (TENS) efficacy for select patients with chronic low back pain, however there is still no consensus regarding efficacy of TENS for treating chronic LBP [8,12-20]. Additionally, the reviews found insufficient quality evidence for recommending for or against the use of high-voltage galvanic therapy, interferential therapy, iontophoresis, percutaneous electrical nerve stimulation (PENS), microcurrent electrical stimulation, and sympathetic electrotherapy for treating chronic low back pain. Similarly, although there is strong anecdotal support, there are no reported quality randomized controlled trials demonstrating efficacy of the H-Wave® Device for symptomatic relief of chronic low back pain. Regardless of the evidence of efficacy of TENS in treating chronic LBP, it is a common modality for treating LBP due to high demand for noninvasive, nonpharmacologic interventions. It is highly prescribed due to low cost and low occurrence of side effects [21]. Identification of electrotherapy treatments with quality evidence of efficacy, low cost, and low adverse effect profile would be expected to result in improved patient function, reduced pain, reduced morbidity, improved productivity, and overall lower health care costs. In this study, we evaluate anecdotal properties of the H-Wave ® device, which is reported to be highly efficacious for many patients, and compares both economically and in safety with achieved TENS treatment protocols.

The H-Wave® Device (Electronic Waveform Lab, Inc) stimulation is an electrotherapy modality. The primary difference between other electrotherapies and H-Wave® is the waveform, with larger pulse durations and uniquely low frequencies. H-Wave® utilizes a bipolar exponentially decaying pulse with frequencies between 1-70Hz and a pulse duration of 5 milliseconds along with some other proprietary factors. The H-Wave® device has received FDA clearance for a number of indications, including home-based treatment of chronic pain, post-surgical pain, circulation, range of motion, and muscle spasms. The mechanism(s) of action for the H-Wave® Device are unique and include nitric-oxide dependent enhanced microcirculation and angiogenesis, stimulation and contraction of muscle fibers within the subdermal lymphatic system, and deactivation of the sodium pump within the nerve fiber [22,23]. While the exact mechanism of LBP treatment is unknown there are multiple mechanisms, including the one that is referenced above that may demonstrate efficacy for treating LBP. Other mechanisms include stimulation of nocireceptors and other nerve types to mask pain and allow patients to improve function.

The intent of this trial is to execute a high-quality^a^ double-blinded randomized controlled clinical trial that compares the efficacy of the H-Wave® Device with a commonly used TENS device and with a control group using a sham electrotherapy device [24]. A well-designed, high-quality trial will provide definable level of evidence for treatment efficacy, and provide a basis for evidence-based recommendation for or against utilization of the use of the H-Wave® device. The results for H-Wave® device, if positive, could significantly impact morbidity by providing a non-invasive, non-pharmacologic treatment for symptomatic relief, and reduce overall disability and health care costs associated with chronic low back pain.

## Methods/Design

### Participants

Subjects will be recruited from University and community practitioners, as well as through media advertisements. Enrollment and treatment will be conducted in clinical/laboratory facilities at the University of Utah’s Rocky Mountain Center for Occupational and Environmental Health.

Potential study subjects identified through the institutional review board (IRB) approved study marketing materials will be screened based on inclusion and exclusion criteria. If all criteria are met, they will be scheduled for a consent, randomization, and initial treatment.

Inclusion criteria for study eligibility includes: ages 18–65 with chronic low back pain (≥3 months duration; a current VAS pain rating ≥5/10; no radiating pain below the knee; ≥75% back or buttock pain rather than lower extremity pain; English speaking, and able to complete and tolerate treatment for the study period.

Exclusion criteria include: Prior home use of H-Wave® Device or TENS. Prior history of spinal fusion or failed spinal surgery syndrome. Laminectomy, laminotomy or discectomy within 12 months of enrollment. Diagnostic or interventional injections or any low back surgeries not mentioned above, including radiofrequency neuroablation within 6 months of enrollment. Current implanted cardiac demand pacemakers, defibrillators, cardiac pumps, spinal stimulators or other implanted electronic devices. Patients using personal home based electrical stimulation devices are excluded to reduce risk of blinding failure. Patients with other concomitant illnesses (e.g., malignancy, osteoporosis) which, in the opinion of the investigator, would preclude successful patient participation will also be excluded. Active psychiatric disorders will be excluded (e.g. use of antipsychotic medication, bipolar disorder, schizophrenia). Patients diagnosed with history of significant mood disorder will be excluded (e.g., depression or anxiety with adequate control would be acceptable). Patients currently are or who become pregnant will be excluded.

Consent will be obtained prior to randomization. Potential study subjects will be given a copy of the consent document and the document will be outlined in detail by a research team member. Potential study subjects will be given opportunities to ask questions prior to signing the consent form and enrolling in the study.

This study has been approved through the University of Utah Institutional Review Board (IRB # 52918). Study participants will receive compensation for participation in this study (Figure 1).

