### Blinding

We will attempt to blind patients and assessors to achieve double blinding. Patients will not be told what electrotherapy techniques are being utilized in this study, only that there are two active electrotherapies out of the spectrum of electrotherapy devices and a sham group. All study materials will be void of the words H-Wave® or TENS. Patient blinding will be accomplished by providing all patients either a H-Wave® device, a fully operation TENS Unit modified to function within a H-Wave® device housing, or a sham electrotherapy device with minimally perceptible electrical current output modified to function within a H-Wave® device housing. Researchers providing the treatment are not blinded. Assessors are blinded and will not be present for the intervention. Participants will be instructed not to reveal or discuss the type of treatment characteristics they are experiencing.

Sham devices will appear to operate in the same exact way as a fully functional electrotherapy device, including battery drain and usage log. At maximal settings, weak electrical current will be flowing to the pads so that the patients may perceive the device as active treatment.

Additional blinding of subjects or treatment within this trial is not possible. The research team will be required to wear color-coded nametags indicating whether or not the researcher is blinded or non-blinded to avoid any confusion at the time of assessments. Efficacy of assessor blinding will be conducted at all onsite assessments by recording assessor’s opinion of treatment arm for each subject.

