There are no accepted standardized protocols found in the literature for TENs treatment of chronic low back pain. There are no trials that demonstrate maximum efficacy of pulse duration, wave type, or frequency. Therefore, the TENS units in this study allow adjustment of amplitude (intensity) only at a fixed frequency of 100 Hz with steady state pulsing. Modulation and pulse modes will be disabled in order to maintain uniformity of electrotherapy protocols. Pad placement will be directed by the provider to provide maximal clinical efficacy. The device is two channel TENS and will be administered by the patient after training by the provider.

The sham or control device will appear to operate in the same exact way as a fully functional TENS device, including battery drain and usage log. Subtherapeutic electrical current will be flowing to the pads so that the patient may perceive it as an active therapy. They will be instructed to use the device for the same duration as active treatments, daily upon waking and before bedtime, and up to two additional treatments during the day as needed (e.g., 4 1-hour treatment sessions). There is no quality evidence that subtherapeutic electrical current provides any clinical benefit over no electrotherapy effectiveness for LBP, however this will likely blind the patients because none of them have ever experienced the H-Wave Device. Blinding of patients is achieved as none will have previously experienced H-Wave, home based TENS therapy, or subtherapeutic electrotherapy. Further, patients are kept blind as to which electrotherapy devices out of the myriad devices on the market, are included in the study and therefore have few preconceived notions to their assigned device.

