#### Intent-to-treat analysis

These data will be analyzed using an intent-to-treat analysis. As H-Wave® Device is not widely utilized in study catchment area it is doubtful that individuals will inadvertently crossover to that arm from the controls. However, that possibility will be both discouraged and tracked.

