## Discussion

Chronic low back pain is a significant issue, resulting in significant costs, lost productivity, and morbidity [1-6]. Therefore, even small improvements in treatment efficacy, particularly for treatments with few side effects, can have a meaningful impact on improving LBP. While there have been some studies assessing the therapeutic effectiveness of TENS, the effect generally is relatively small improvements in chronic LBP as compared to sham treatment. The use of two comparison arms in this study, both TENS and sham treatment, allows for comparisons of experimental device with both TENS as well as sham treatment.

Blinding within this study is a significant strength. All devices are identical in appearance, weight, display, charge time, and sound. It is anticipated that complete blinding of the assessors and patients will be achieved. Care will be taken to limit contact between participants, e.g. schedule participants one at a time so they are not waiting in the same room together. All treatment questions will be directed to the interventionalists, as to maintain blinding of the assessors. Additionally, this protocol outlines concealing the treatment allocation by using opaque envelopes that appear identical. The utilization of a complex randomization schedule is another strength that may ensure equality of treatment groups at baseline. The intent-to-treat analysis may account for unequal dropout between groups and any contamination that may occur.

Potential weaknesses include the possibility of high dropout in one or more treatment arm. To combat this, we are offering incentives and encouraging participants to continue for the entire duration of the study. There is the possibility of a randomization failure, which cannot be overcome. Additionally, due to the nature of the treatment, specifically the differences between the experimental treatment and the TENS treatment, it was not feasible to blind the interventionalist. To address this all interventionalists will undergo strict training and re-standardization based on the treatment protocol. This training will stress treating all patients similarly with regards to demeanor and contact time, regardless of their randomized treatment arm.

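### The patient blind is declared achieved because no patient has ever experienced H-Wave, but the entry criteria exclude only home use, so that ground is not secured

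*Protocol article*

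**What the plan says.** **Entry criteria (Participants).** Two exclusions concern earlier or current electrotherapy. The first is "Prior home use of H-Wave® Device or TENS". The second is "Patients using personal home based electrical stimulation devices are excluded to reduce risk of blinding failure". Both are limited to the home, and the second shows that protecting the blind is the purpose.

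**Ground for the blind (Treatment protocols).** On the sham device the article says that "this will likely blind the patients because none of them have ever experienced the H-Wave Device". A sentence later it concludes: "Blinding of patients is achieved as none will have previously experienced H-Wave, home based TENS therapy, or subtherapeutic electrotherapy". In that conclusion the home qualifier is attached to TENS and not to H-Wave or to subtherapeutic electrotherapy.

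**Strength of the claim elsewhere.** The Blinding section speaks only of an attempt to blind patients and assessors, and adds that "All study materials will be void of the words H-Wave® or TENS". The Discussion goes further: "It is anticipated that complete blinding of the assessors and patients will be achieved". The endnote gives patient blinding the full point in the quality score.

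**Local use of H-Wave (Intent-to-treat analysis).** "As H-Wave® Device is not widely utilized in study catchment area it is doubtful that individuals will inadvertently crossover". This is an argument about crossover during the trial, not an entry rule.

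**The concern.** The article presents lack of earlier experience as the reason the patient blind works. That reason is only as good as the criterion that enforces it, and the criterion is narrower than the reason. A patient with chronic back pain who received H-Wave from a practitioner, and never took a device home, is eligible under the text as written.

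The ODI (primary outcome) and the pain VAS (main secondary endpoint) are both reported by the patient, so the comparisons with sham, and between the two active devices, depend on patients not knowing what they have. A report that repeated the article's wording would claim a property of the enrolled sample that nobody had checked at entry.

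**Working it through.** No arithmetic in the plan bears on this point, so the check is a comparison of texts, followed by what can and cannot be said about size.

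**1. Criteria against claim, exposure by exposure**

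| Earlier exposure | Participants section | Treatment protocols section | Claim secured? |
|---|---|---|---|
| H-Wave at home | excluded | none has had it | yes |
| H-Wave in a clinic | not excluded | none has had it | **no** |
| TENS at home | excluded | none has had it | yes |
| TENS in a clinic | not excluded | no claim made | no contradiction |
| Subtherapeutic electrotherapy | not named in any criterion | none has had it | **no** |

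**2. Does another provision close the gap?** The remaining exclusions concern surgery, injections, implants, other illness, psychiatric history and pregnancy. None touches earlier clinic electrotherapy. The section on interventions not allowed governs treatment during the trial, not history. The remark on local use makes clinic H-Wave uncommon but does not make it zero.

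**3. What could an exposed patient notice?** All three arms use an H-Wave housing, and the Discussion says the devices match in look, weight, screen, charging and sound. The casing therefore cannot show the arm. Sensation could. H-Wave patients work up towards the highest intensity they can comfortably reach, TENS runs at a fixed 100 Hz with only intensity adjustable, and sham output is barely perceptible. Someone who remembers H-Wave could notice that TENS or sham is not H-Wave. This is a possibility, not a certainty.

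**4. Size and direction of bias.** Two inputs would be needed: the share of enrolled patients with clinic H-Wave experience, and the change in reported ODI when such a patient draws a conclusion about the device. The article gives neither. Direction is also open, because an H-Wave-experienced patient could notice the difference in the TENS arm as well as in the sham arm.

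**5. Precision of a sensitivity analysis without clinic-exposed patients.** From the sample size section: SD 15 and 25 evaluable patients per arm. Formula: standard error of a difference in means = SD × √(2/n). The shares exposed to any clinic electrotherapy are assumptions.

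- Nobody removed: 15 × √(2/25) = 4.2 points.
- 10% removed, n = 25 × 0.90 = 22.5: 15 × √(2/22.5) = 4.5 points.
- 30% removed, n = 25 × 0.70 = 17.5: 15 × √(2/17.5) = 5.1 points.

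These are unadjusted two-group figures. The planned mixed model may do better, but the comparison would remain imprecise against the 10-point difference used in planning.

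**The case against.** The strongest reply is that this is one over-broad sentence affecting very few people. H-Wave is said to be little used in the catchment area ("As H-Wave® Device is not widely utilized in study catchment area"), so the number of clinic-exposed patients may be near zero. The article also has real safeguards. Patients are told only that two active electrotherapies and a sham are in use, without names. Weak current flows in the sham. All patients are warned that stimulation may stay below what they can feel, so a faint or unfamiliar sensation need not mean sham.

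Most of this stands. It limits the likely effect and rules out treating recognition as a fact. It does not repair the reasoning: the article infers that blinding is achieved from a universal absence of H-Wave experience, and low local use cannot establish a universal absence. The rarity that makes the gap small also makes it cheap to close.

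It may also be said that a journal article condenses the full protocol. That would excuse an omission. Here the criterion, its purpose and the conclusion are all printed, and the conclusion is wider than the criterion. The article describes a check of blinding for assessors only; a check for patients may stand in the full protocol, and its absence is not counted here.

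**Conclusion.** The point holds as a mismatch between a stated ground and the criterion meant to secure it. It covers clinic-delivered H-Wave and, in the same sentence, subtherapeutic electrotherapy. The number of patients affected is probably small, on the article's own remark about local use, and the bias in ODI and VAS cannot be quantified or signed from the document.

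A reader might infer more in four ways, none of which the document supports.

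- *That clinic TENS exposure is also a contradiction.* It is not, since both sections limit TENS to home use. The Background calls TENS common and highly prescribed, so clinic TENS is a residual risk to the blind, partly mitigated by the warning about sub-sensory current.
- *That the sham mean shifts by 0.5 to 1.5 ODI points.* This is an assumed 10 to 30% exposed times an assumed 5-point change (0.10 × 5 = 0.5; 0.30 × 5 = 1.5). Both inputs are invented, the sum takes every exposed sham patient as unblinded, and the exposure range suits clinic TENS rather than rare H-Wave.
- *That the housing unblinds.* It is the same in every arm.
- *That screening by device name leaks the names.* No screening script is shown, and the article keeps both names out of study materials.

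**What to change.** 1. In Participants, extend the exclusion to any prior H-Wave treatment, at home or in a clinic, and keep the existing home-use exclusions for TENS and personal stimulators.
2. Record prior clinic electrotherapy (yes/no) for every patient before allocation. Repeat the 4-week ODI comparison without the patients who answer yes, labelled as a sensitivity analysis. This leaves clinic-TENS patients in the trial and shows whether the result depends on them.
3. In Treatment protocols, replace the statement that the blind is achieved with one that claims only what the criteria ensure. Remove the reference to subtherapeutic electrotherapy or support it with a criterion. Bring the Discussion's expectation of complete blinding into line with the more cautious Blinding section.

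The cost is a change to one criterion, one baseline item, some rewording and a few additional screen failures. The sensitivity analysis will have low precision, so it should be read as a check on consistency and not as a test.
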